## Procedures and flow chart

**

## Biological sampling procedures

### Handling, storage, and destruction of biological samples

At each study visit the following sampling will occur: one serum tube (9 mL) for analysis of antibodies to SARS-CoV-2 and three gel-free lithium heparin tubes (24 mL) for analysis of interferon-gamma and other markers. The biological material will be coded with a code key. the study will have access to the biological material for one year after the project is completed so that all analyzes have time to be performed. Thereafter all samples will be stored at Biobank Väst (co-administered by Region Västra Götaland and Sahlgrenska Academy).

## End of Study

The end of trial will be on March 1, 2024 by which time all data and sampling will have been collected and completed for the study population.

# Subject selection

- 1. Inclusion criteria

To be included in the study, subjects must meet the following criteria:

- The subject has given written consent to participate in the study.
- The subject must be woman or man aged 18 years or older undergoing vaccination against COVID-19 in Region Västra Götaland in accordance with clinic routine and regional prioritization.

## Exclusion criteria

Subjects must not be included in the study if any of the following criteria are met:

- Inability to give written informed consent
- Inability to undergo blood sampling, for example lack of suitable blood vessels for sampling

## Screening

Suitable study participants will be recruited from patients attending clinics at the Sahlgrenska University Hospital as well as healthy personnel working at the Dept. of Microbiology and Infectious Diseases Clinic at Sahlgrenska University Hospital.

Subject eligibility (that subjects fulfill all inclusion criteria and do not meet any exclusion criteria) is established before inclusion, treatment, or randomization.

## Withdrawal criteria

- The study subject may choose to discontinue the study at any time
- If they choose to *discontinue* their participation in the study, they do not have to state why, nor will it affect their future care or treatment. Cancelation of participation is easily performed by contacting the person responsible for the study.

# Study treatments

## Description of investigational product(s)

The approved COVID-19 vaccines will be used according to the approved indication. The relevant Summary of Product Characteristics (SmPC) is being submitted with the application.

## Randomization

No randomization will be performed in this study as the researchers involved in this study have no influence or input with regards to which COVID-19 vaccine the participants receive, the number of vaccine doses, nor the timepoint of vaccination. The vaccination will be performed by healthcare providers in Region Västra Götaland in accordance with national and regional prioritization as well as the clinic routine.

Subjects are included consecutively as they are found to be eligible for inclusion in the study. If a subject discontinues their study participation, their subject code will not be reused, and the subject will not be allowed to re-enter the study again.

## Blinding

The study is open and not blinded.

# Methods for measurement of endpoints for clinical efficacy and safety

- 1. Methods for measurement of endpoints for clinical efficacy

Levels achieved using the methods below will be monitored immediately before the 1^st^ and 2^nd^ vaccine doses, 4 weeks post-2^nd^ vaccine dose, and then every 3 months for 2 years for the following analyses:

1. anti-RBD Spike IgG quantitative serology calibrated against a WHO standard (Abbott)
2. a novel rapid spike interferon-γ release assay
3. a novel rapid spike activation-induced marker assay
   1. Primary endpoint (variable)

The primary endpoints (variables) are the levels achieved using the abovementioned assays, which will be monitored immediately before the 1^st^ and 2^nd^ vaccine doses, 4 weeks post-2^nd^ vaccine dose, and then every 3 months for 2 years. This study is an open phase IV post marketing surveillance, observational prospective cohort study.

- 1. Methods for measurement of endpoints (variables) for clinical safety

The endpoint(s) (variables) for clinical safety will be the reported adverse events (AE) and serious adverse events (SAE). This analysis will be performed continuously during the study.

# Handling of Adverse Events and Serious Adverse Events

Adverse events (AE) and serious adverse events (SAE) will be handled according to established health care standard reporting system.

- 1. Suspected Unexpected Serious Adverse Reaction (SUSAR)

A Suspected Unexpected Serious Adverse Reaction (SUSAR) is as stated by the abbreviation a suspected unexpected serious adverse reaction. This infers that the event is likely related to the administered IMP but that the occurrence of the event is unexpected and the adverse events that are not included in the Investigator’s Brochure (IB) or SmPC.

If sponsor detects a SUSAR this should be reported. When reporting a SUSAR (in English) the EU-common form CIOMS should be used.

- 1. Reporting of Suspected Unexpected Serious Adverse Reactions (SUSAR)

Those SAE which comes to the knowledge of the sponsor and is assessed to be SUSAR should be reported via a [CIOMS form](https://cioms.ch/wp-content/uploads/2017/05/cioms-form1.pdf) to the European Medicines Agency (EMA) EudraVigilance database according to the specified time frames.

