# List of used acronyms and abbreviations

| **Abbreviation** | **Term/Explanation** |
| --- | --- |
| AE | Adverse Event = any untoward medical occurrence |
| AR | Adverse Reaction = adverse event, that is each unfavorable and unexpected reaction to a study treatment, regardless of dose |
| CRF | Case Report Form |
| DSUR | Development Safety Update Report = annual safety report |
| GCP | Good Clinical Practice |
| ICH | International Council for Harmonization |
| IMP | Investigational medicinal product |
| ITT | Intention-to-treat = including all data from all subjects who have participated in the study |
| LVFS | Läkemedelsverkets författningssamling (in English: Swedish Medical Products Agency’s statutes) |
| PP | Per Protocol analysis = including only data from subjects who have completed the study completely in accordance with the protocol, with no deviations from the protocol |
| SAE | Serious Adverse Event = serious untoward medical occurrence. SAEs include all serious events independent of whether they have a suspected causal relationship to the IMP or not. |
| SmPC | Summary of Product Characteristics |
| SUSAR | Suspected Unexpected Serious Adverse Reaction |
|  |  |
|  |  |

#

1. Synopsis

| EudraCT number: 2021-000349-42 |
| --- |
| Title: Evaluation of the Durability of Immune Responses to SARS-CoV-2 Using Novel Rapid Spike Interferon-Gamma Release and Activation-Induced Marker Assays and Anti-Spike IgG Following COVID-19 Vaccination |
| Study code: DurIRVac |
| Short background/Rationale/Aim: Vaccination against COVID-19 has now commenced in Sweden, although the durability of immune responses following vaccination for COVID-19 remains unclear. |
| Primary objective: To evaluate the durability of immune responses following vaccination for COVID-19 among immunocompromised, cirrhotic, renal insufficient and healthy participants using novel rapid spike interferon-γ release and activation-induced marker assays and anti-spike IgG serology, aiming at identifying correlates of vaccine-induced protection. |
| Study design: Phase IV post marketing surveillance, observational prospective cohort study |
| Study population: Immunocompromised, cirrhotic, renal insufficient and healthy participants |
| Number of subjects: 500 |

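### The protocol gives two causality thresholds for a SUSAR in consecutive sentences, *suspected* and then *likely related*, so the trigger for EudraVigilance reporting is unclear

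*Protocol*

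**What the plan says.** The Protocol defines a SUSAR in the section Handling of Adverse Events and Serious Adverse Events. The first sentence reads: "A Suspected Unexpected Serious Adverse Reaction (SUSAR) is as stated by the abbreviation a suspected unexpected serious adverse reaction". The second explains it: "This infers that the event is likely related to the administered IMP but that the occurrence of the event is unexpected". The same sentence ties expectedness to "the adverse events that are not included in the Investigator’s Brochure (IB) or SmPC".

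The reporting subsection then makes the classification operative. An SAE that reaches the sponsor and "is assessed to be SUSAR should be reported" to EudraVigilance on a CIOMS form, within the specified time frames.

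The List of used acronyms and abbreviations expands SUSAR as "Suspected Unexpected Serious Adverse Reaction". It defines an AE without any causal or expectedness condition ("Adverse Event = any untoward medical occurrence") and says that SAEs include every serious event whether or not a causal link is suspected. Its entry for AR reads: "Adverse Reaction = adverse event, that is each unfavorable and unexpected reaction to a study treatment, regardless of dose".

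Two further statements limit the point. The adverse-event section opens by placing all AEs and SAEs under the established health care reporting system. The section on methods for measuring endpoints makes reported AEs and SAEs the clinical safety endpoint, analysed continuously.

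**The concern.** A reporting trigger should let two assessors with the same judgement of an event reach the same decision. This one does not. In ordinary usage a causal link can be suspected without being likely. The first sentence takes in such an event and the second leaves it out. The second sentence is the one that explains the term, so an assessor may well apply it.

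At stake is the one step that the protocol attaches to SUSAR status: expedited reporting to EudraVigilance. The Statistics section plans five groups of about 100, four of which have cirrhosis, impaired kidney function, an organ transplant or other immune impairment. That is 4 × 100 = 400 of about 500 participants. It is a reasonable expectation, though not a statement in the protocol, that serious events in such patients often have competing explanations. If so, suspected but not likely is a foreseeable judgement, and it is the one on which the two sentences disagree.

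**Working it through.** No arithmetic applies: the point rests on no rate, sample size or error level. The check sets the definitions side by side and then takes types of event through them.

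**Causality wording in the Protocol**

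| Place | Causal condition |
| --- | --- |
| Abbreviation list, SUSAR | suspected |
| Abbreviation list, SAE | none; mentions a suspected relationship as the distinction that does not matter for an SAE |
| SUSAR subsection, first sentence | suspected |
| SUSAR subsection, second sentence | likely related |
| SUSAR reporting subsection | none of its own; relies on the SUSAR assessment |

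The protocol's own causality word is *suspected*, used three times. *Likely* appears once, in the sentence that claims to explain the term. The text gives no causality scale that would bring the two together.

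**Types of event under the wording as written**

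1. *Serious, unlisted, judged likely related.* It meets both sentences. It is a SUSAR and goes to EudraVigilance.
2. *Serious, unlisted, suspected but not judged likely.* It meets the first sentence and fails the second. Its SUSAR status, and so its expedited reporting, is ambiguous. It remains an SAE, is handled under the health care reporting system and counts in the safety endpoint.
3. *Serious, listed in the IB or SmPC.* It is not a SUSAR, as the expectedness clause intends. It remains an SAE and is counted.
4. *Non-serious, listed.* It fails the AR entry because it is not unexpected. It remains an AE and is counted.

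The conflict changes a possible reporting decision only in case 2.

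**The AR entry.** It equates a reaction with an adverse event, although the AE entry requires no causal link. It also makes unexpectedness part of every adverse reaction, so that the separate word *unexpected* in SUSAR adds nothing. Because a SUSAR must be unexpected anyway, stating the requirement twice excludes no further event. In the text shown, no endpoint, rule or count uses AR as a category of its own. The entry is badly worded but has no operational effect.

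**The case against.** The strongest reply is that the first sentence is the definition and the second a loosely worded gloss, as its use of *infers* for *implies* suggests. The Ethics section also commits the study to ICH-GCP and current regulations, so the gloss is not the only standard that binds the assessor. This stands in part: the text makes the outcome for a suspected-only event ambiguous, and does not settle that it goes unreported. It does not remove the defect. A trigger that depends on the assessor overlooking its explanatory sentence needs correction, and a general commitment to regulations does not say which of the two sentences governs.

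A second reply is that this is an observational study whose researchers choose neither vaccine, dose number nor timing, so the matter is editorial. That is fair for the AR entry. It is not fair for the SUSAR sentence, because the protocol itself commits the sponsor to SUSAR reporting.

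Three stronger readings are tempting, and the documents do not support them.

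- A reader might infer that suspected-only events, and all listed reactions, escape the safety rules altogether. They do not: AEs and SAEs are defined without regard to causality or expectedness, are all handled, and form the safety endpoint. Listed reactions are properly outside SUSAR.
- A reader might infer that known reactions disappear from a count of adverse reactions. The protocol contains no such count.
- A reader might want to state what share of reportable cases would be withheld. Nothing in the document anchors one. Nor does it say where the health care reporting system sends its reports, so it cannot be said that these events would never reach EudraVigilance by another path.

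**Conclusion.** The point holds in a limited form. The protocol sets two different causality thresholds for a SUSAR in adjacent sentences, and the only route to EudraVigilance that it describes depends on that classification. A literal reading of the second sentence could keep a serious, unlisted event that is suspected but not judged likely out of expedited reporting. The event would still be handled and counted as an SAE.

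The size is one class of event. The share of suspected, unlisted serious events in that class could in principle lie anywhere from none to all, depending on how assessors judge causality, and the protocol gives no figure to narrow this. The conclusion assumes only that *likely* is stricter than *suspected* in ordinary use, and that an assessor may follow the explanatory sentence. Definitions and reporting triggers are protocol content, and this is a stated contradiction, so a separate analysis plan would not resolve it. The sentence should be corrected. The AR entry alone would be clerical.

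**What to change.** In the SUSAR subsection, use one threshold that matches the protocol's own term: replace the words *likely related* with a statement that *a causal relationship to the administered IMP is suspected*. Leave the expectedness clause (not in the IB or SmPC) as it is. This costs one sentence, and in operation possibly a few more CIOMS reports.

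In the same amendment, delete *unexpected* from the AR entry in the abbreviation list, so that expectedness belongs only to the SUSAR definition. This costs one word and has no effect on what is reported or counted.

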# Statistics

This study is an open phase IV post marketing surveillance, observational prospective cohort study to determine the sustainability of immune responses to SARS-CoV-2 following natural infection and vaccination. As there are currently very few preliminary data, it is difficult to provide a statistical basis for the study population. We intend to initially examine the immune response of approximately 100 healthy researchers, 100 researchers with cirrhosis, 100 researchers with impaired kidney function, 100 researchers who have undergone organ transplantation and 100 researchers with impaired immune systems for other reasons.

# Quality Control and Quality Assurance

Quality Control (monitoring) and Quality Assurance (auditing) will be performed by Gothia Forum, [name]

telephone [name])
**E-post:** [[contact]](mailto:[contact])

## Quality Assurance and Sponsor oversight

The quality assurance systems and methods deemed appropriate by Gothia Forum will be used to assure that the study will ensure and control the quality as well having oversight of the study’s quality. This applies for the communication plan, training of study personnel, working manuals, meetings, central/local monitoring, audits etc.

The participant will provide an extra serum tube (9 mL) and three lithium-heparin tubes without gel (24 mL) at each sampling other than that included in routine clinical practice. The discomfort of sampling and the invasion of integrity is considered minor. All statistical processing, compilation and reporting of the material takes place with the help of a decoded database in which the participants' identities remain unknown.

The scientific value of the study is judged to be great. The discomfort of sampling and the invasion of integrity is considered minor. Participants can relatively easily decide for themselves and thus make an informed decision about possible participation. Thus, the risk to subjects posed by participating in the study is considered low.

## Monitoring

The study will be monitored by an independent monitor (Gothia Forum) before the study begins, during the study conduct, and after the study has been completed, so as to ensure that the study is carried out according to the protocol and that data is collected, documented, and reported according to ICH-GCP and applicable ethical and regulatory requirements. Monitoring is performed as per the study’s monitoring plan and is intended to ensure that the subject’s rights, safety, and well-being are met as well as data in the Case Report Form (CRF) are complete, correct, and consistent with the source data.

## Source data

The investigator must keep source documents for each subject in the study. A document describing what has been classified as source data in the study should be included in the Investigator Site File (ISF). The investigator must ensure that all source documents are accessible for monitoring and other quality control activities.

Source data is defined before study start at each individual site. The CRF is defined as source data in cases where data is not registered elsewhere, e.g., inclusion and exclusion criteria.

# Ethics

## Compliance to the protocol, GCP and regulations

The study will be performed in compliance with the study protocol, the Declaration of Helsinki, ICH-GCP (Good Clinical Practice) guidelines and current national and international regulations governing this clinical trial. This is to ensure the safety and integrity of the study subjects as well as the quality of the data collected.

## Ethical review of the study and procedure for informed consent

The final study protocol for clinical trials must be approved, as a part of the application for a permit for clinical trials, by both the Swedish Ethical Review Authority (Etikprövningsmyndigheten) and the Swedish Medical Products Agency before the trial can be conducted. The final version of the informed consent form and other information provided to subjects, must be approved or given a written positive opinion by the Swedish Ethical Review Authority.

The principal investigator at each site shall ensure that the subject is given full and adequate oral and written information about the study, its purpose, any risks and benefits as well as inclusion and exclusion criteria. Subjects must also be informed that they are free to discontinue their participation in the study at any time without having to provide a reason. Subjects should be given the opportunity to ask questions and be allowed time to consider the provided information. If the person chooses to participate, both the subject and the investigator shall sign the informed consent form. A copy of the subject information as well as the informed consent form shall be provided to the subject. The subject’s signed and dated informed consent must be obtained before performing any study-specific activity in the study. Each subject who participated in the study will be identified by a subject number on a subject identification list. The subject agrees that monitors, auditors, and inspectors may have access to their medical records and other source data. If new information is added to the study, the subject has the right to reconsider whether he/she will continue their participation.

# Collection, handling, and archiving data

Subjects who participate in the study are coded with a specific study identification number. All subjects are registered in a subject identification list (subject enrolment and identification list) that connects the subject’s name and personal number with a study identification number.

All data will be registered, managed, and stored in a manner that enables correct reporting, interpretation, and verification. The complete Trial Master File, as well as source documents, will be archived for at least 2 years after the study is completed. Source data in the medical records system is stored and archived in accordance with the respective hospital regulations.

## Case Report Form (Forskningspersonsformulär)

A Case Report Form (CRF) is used for data collection. The investigator must ensure that the registered data is correct, complete, and that reporting takes place according to the timelines that have been predefined and agreed. The investigator signs the completed CRF. A copy of the completed CRF will be archived at the study site.

# Notification of study completion, reporting, and publication

The Swedish Medical Products Agency shall be informed of the study’s completion at latest 90 days after study end, through submission of a ”Declaration of End of Trial Notification” form.

Within one year after the study is completed, the results shall be analyzed, a clinical study report with individual data shall be prepared, and the study results shall also be reported in the EudraCT database.

